**Study Site and population**

This study will be done inthe Dhaka Hospital at icddr,b. This is the largest diarrheal disease hospital in the world. According to recent data, approximately 152,000 patients of all ages are treated here in a year (25). Among the treated patients, 62% are under the age of 5 years (25). In this study, we will enroll diarrheal children with SAM aged 9-24 months of both gender attending a longer stay unit (LSU).

**Study Duration:** 24 months

**Eligibility Criteria**

Inclusion criteria

- Diarrheal children with SAM aged 9-24 months
- Signed informed consent by the guardian/caregivers

Exclusion criteria

- Severe sepsis or Septic shock
- Patients already taking medications containing L- carnitine
- Children with Tuberculosis
- Children with congenital defects or chromosomal anomalies
- Children with a diagnosed case of Thalassemia
- Children with an active or previous history of convulsion

**Intervention**

Investigational products:

- L- carnitine oral solution (100mg/ml) for Group A
- Placebo for Group B- Oral solution identical in appearance and taste to the active preparation (L-carnitine syrup) with no therapeutic value

**Dosage:** 100 mg/kg/day, divided into 3 doses per day for 15 days.

**Packaging and labeling:** The investigational product will be dispensed in a 100ml bottle.

**Drug accountability**

The L-carnitine syrup formulation will be provided for 15 days to study participant at nutritional rehabilitation unit (NRU) under controlled set-up. They will be evaluated by measuring the rate of weight gain at 15 days of supplementation and 180 days of completion of supplementation. A telephonic follow-up will be done on after 15 days of completion of supplementation. Study investigator will update accountability records of the investigational product according to ICH E6, GCP guideline. Investigational product will not be provided to any third party.

**Workflow for enrolment:**

**
[figure not shown]
**

**Figure 2. Work flow for the participants enrolled in the study**

**Screening, Consenting and Baseline Data Collection**

The research staff will screen all the participants within the defined age groups according to the eligibility criteria. Participants fulfilling the eligibility criteria will be brought to study physician for clinical assessment. Upon signing a written informed consent, the participant will be enrolled by the study physician. Case record form (CRF) will be used to collect relevant information such as medical history including nature and duration of illness, medication for current illness; socio-demographic characteristics such as age, sex, religion, parental age with education, parent’s occupation, monthly family income, number of siblings etc. Information will also be collected about child’s feeding practice such as- history of breast feeding, formula or other complementary feeding, immunisation status, family history of tuberculosis, recent respiratory tract infection of any family members and past history of child’s pneumonia would be recorded.

**Randomization:**

In this proposed study we will use block randomization in following method:

- We will randomize the study participant in a way so that balance can be maintained across the treatment group and placebo group. Each “block” would have a specified number of randomly ordered treatment and placebo assignments.
- It will be a double blinded study. We both the investigators and study participants and their care givers won’t know who will be receiving the particular treatment.
- We have a plan to make 17 blocks- 8 blocks of size 4, 4 blocks of size 6, 4 blocks of size 8, 1 block of size 10.

[figure not shown]

**Figure 3: Block Randomization**

| Criteria |  | Male | | Female | |
| --- | --- | --- | --- | --- | --- |
| WLZ score ≤3SD, or/and  MUAC <115 mm | Block Size 4 | AABB | BBAA | ABAB | BABA |
| Block Size 6 | AAABBB | BBBAAA | ABABAB | BABABA |
| Block Size 8 | AAAABBBB | BBBBAAAA | ABABABAB | BABABABA |
| Block Size 10 | ABABABABAB | | | |
| Bilateral Pedal Edema | Block Size 4 | AABB | BBAA | ABAB | BABA |

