**Or,**

We will assign participants to the intervention or the control arm using permuted block randomization method with concealment to ensure that the allocation is not made before the participant has given their consent and joined the study. A random allocation sequence will be generated using a computerized random allocation system for permuted block randomization to ensure comparable allocation numbers at a certain equally spaced points in the sequence of patient assignment. A parallel type of randomization will be used. Reasonably large blocks with variable block sizes will be constructed to reduce the predictability. Random assignment will be prepared in advance by an independent researcher from icddr,b, who has no involvement with the trial.

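### The protocol joins two incompatible randomization methods with 'Or,', and the first prints fixed, patterned block sequences with the arm code disclosed

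*Protocol*

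**What the plan says.** The protocol's Randomization section describes allocation twice.

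**First method.** Each block "would have a specified number of randomly ordered treatment and placebo assignments". The plan is specific: "We have a plan to make 17 blocks- 8 blocks of size 4, 4 blocks of size 6". Four further blocks have size 8 and one has size 10. The table under Figure 3 then gives explicit sequences by sex and by type of malnutrition:

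- WLZ/MUAC rows: two sequences per sex for each of sizes 4, 6 and 8, such as "Block Size 4 | AABB | BBAA | ABAB | BABA" and "Block Size 8 | AAAABBBB | BBBBAAAA | ABABABAB | BABABABA". The first two entries in each row are for boys, the last two for girls.
- One block not split by sex: "Block Size 10 | ABABABABAB".
- Oedema row: the same four size-4 sequences again.

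The letters are not neutral codes. The Intervention section lists "L- carnitine oral solution (100mg/ml) for Group A" and placebo for Group B, and the sample-size table in the RRC application form names Group A as the intervention arm.

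**Second method.** After the single word 'Or,' the protocol describes permuted blocks with concealment, a computer-generated list and preparation in advance by a researcher with no part in the trial. It adds: "Reasonably large blocks with variable block sizes will be constructed to reduce the predictability". This paragraph mentions no strata.

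Nothing states which method is operative.

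**The concern.** The two methods cannot both be followed. A list in which every balanced order of a block is equally likely is not a list built from two mirror-image orders per sex and size. The first method also contradicts itself, because it promises random order within blocks and then fixes that order in print.

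The stake is allocation concealment. A team using the Figure 3 table would comply with the protocol as written, yet would hold a document showing the possible treatment sequences in clear. A sound scheme limits the damage when one allocation is learned or guessed, through a code break, a serious event or a post-treatment carnitine value. Patterned blocks let that knowledge carry forward to later children. Bias in who is enrolled next cannot be repaired in the analysis.

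**Working it through.** **1. Does the table match the plan?**

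| Size | Blocks planned | Sequences printed | Slots |
|---|---|---|---|
| 4 | 8 | 4 (WLZ/MUAC) + 4 (oedema) = 8 | 32 |
| 6 | 4 | 4 | 24 |
| 8 | 4 | 4 | 32 |
| 10 | 1 | 1 | 10 |
| Total | 17 | 17 | 98 |

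The sequences hold 49 A and 49 B, which is the planned sample size of 49 per group. A full match on count, sizes, total and balance points to a working list, not an illustration.

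**2. How much of the order is left to chance?** The number of balanced orders of a block of size 2m is C(2m, m): 6, 20, 70 and 252 for sizes 4, 6, 8 and 10. The table uses 2 per sex for sizes 4, 6 and 8, and 1 for size 10.

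**3. Predictability under the printed table.** These assumptions are not stated in the protocol: each printed block is used once, blocks come in random order within each sex-by-stratum list, the block of 10 is a separate list, the reader knows the table, and earlier allocations in the list are known or guessed. Enumerating all block orders (6! = 720 for each WLZ/MUAC list, 2 for each oedema list) and making the best guess at every slot gives:

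| List | Slots | Expected correct | Fully determined |
|---|---|---|---|
| Boys, WLZ/MUAC | 36 | 31.77 | 26.17 |
| Girls, WLZ/MUAC | 36 | 33.50 | 27.00 |
| Boys, oedema | 8 | 7.50 | 7.00 |
| Girls, oedema | 8 | 7.50 | 7.00 |
| Block of 10 | 10 | 10.00 | 10.00 |
| Total | 98 | 90.27 (92%) | 77.17 (79%) |

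**4. The same under true permuted blocks.** With block sizes known and earlier allocations seen, the expected number of correct guesses per block of 2m is m + 2^(2m−1)/C(2m, m) − 0.5. That is 2.833, 4.100, 5.329 and 6.532 for sizes 4, 6, 8 and 10.

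Total: 8 × 2.833 + 4 × 4.100 + 4 × 5.329 + 6.532 = 66.9, and 66.9/98 = 68%. About 24.7 of 98 slots (25%) are determined.

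**5. Does the block of 10 drive the gap?** Without it, the table gives (90.27 − 10)/88 = 91% and true blocks give (66.91 − 6.53)/88 = 69%. The gap is essentially unchanged.

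**6. With the blind intact.** Every sequence in the four sex-by-stratum lists has its mirror image in the same list. With block order random and unknown, each slot is A with probability exactly 0.50. Enumerating the two 36-slot lists confirms this. Only the block of 10 could be called in advance, and only by someone who knows that it is in use.

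**7. One leaked allocation.** In the 36-slot lists, with one arm known at a known position and nothing else, the best guess for the next child is right 77% of the time for boys and 91% for girls. For any other child in the list it is right on average 56% (boys) or 64% (girls).

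**The case against.** The strongest reply is that the second method is sound and may be the one intended. If so, none of the figures above applies. That is correct, and it is why the point concerns an unresolved choice and not the trial's settled design. It does not remove the defect, because 'Or,' leaves the table available.

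A reader might infer that allocation is simply predictable. The documents do not support this. The trial is double-blind with a placebo identical in appearance and taste, and step 6 shows that the printed lists give nothing away until earlier allocations leak.

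A reader might also infer that one known arm reveals the rest of its block. That holds only where block boundaries are known, or in the oedema lists, where just two lists of eight exist (16 of 98 slots). Step 7 shows the weaker result elsewhere.

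The 92% rests on usage rules that the protocol does not state, and a figure in this section was not available to this review and may explain usage. The table ties the block of 10 to neither sex and gives it no position; shuffled among other blocks, it would not be known outright.

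Nor do the documents say that the same staff control enrolment, discharge and withdrawal. Research staff screen, the study physician enrols, discharge follows set anthropometric criteria, and no one is named as deciding withdrawals. No section says that carnitine results reach enrolling staff during recruitment.

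**Conclusion.** The Randomization section is wrong as written. It offers two methods that exclude each other, and the first contradicts its own promise of random order by printing 17 patterned sequences with the treatment code disclosed. These facts need no assumption.

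The size is conditional. If the table is used as set out in step 3 and earlier allocations become known or guessed, about 92% of assignments can be guessed, against about 68% for true permuted blocks of the same sizes. With the blind intact and block order random and unknown, there is no predictability outside the block of 10, and that block is predictable only if it is known to be in use. The correction should be made before enrolment, since concealment cannot be restored afterwards.

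**What to change.** In the Randomization section, delete the block counts, the Figure 3 sequence table and the word 'Or,'. Make the computer-generated method the only one, and add that block sizes vary at random, that all balanced permutations of a block are equally likely, and that block sizes and sequences are withheld from recruiting staff. If stratification by sex and oedema is still intended, say so in that paragraph, because at present only the table implies it.

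The cost is protocol wording. The paragraph being kept already provides for the computerised system and the independent researcher, so no further children, staff or procedures are needed.

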| 1. Will the consent be obtained from the study participants for use of the preserved specimen for other initiative(s) unrelated to this study, without their re-consent? | | | | Yes  No  Not applicable | | | | | |
| 1. Will the specimens be shipped to other country/ countries?   If yes, name of institution(s) and country/countries. | | | | Yes  No  Not applicable  Name ____________________________________ | | | | | |
| 1. If shipped to another country, will the surplus/unused specimen be returned to icddr,b?   If the response is ‘no’, then the surplus/unused specimen must be destroyed. | | | | Yes  No  Not applicable | | | | | |
| 1. Who will be the custodian of the specimen at icddr,b? | | | | [name] | | | | | |
| 1. Who will be the custodian of the specimen when shipped outside Bangladesh? | | | | Not applicable | | | | | |
| 1. Who will be the owner(s) of the specimens? | | | | icddr,b | | | | | |
| 1. Has a MoU been signed with regards to collection, storage, use and ownership of specimen?   If the response is ‘yes’, please attach a copy of the MoU.  If the response is ‘no’, appropriate justification should be provided for not signing a MoU. | | | | Yes  No  Not applicable | | | | | |
| **Proposed Sample Size:**  Sub-group (Name of subgroup e.g. Men, Women) and Number   | Name | Number | | --- | --- | | (1) Group A (Intervention arm) | 49 | | (2) Group B (Control arm) | 49 | | **Total sample size** | 98 | | | | | | | | | | |
| **Determination of Risk: Does the Research Involve (Check all that apply**)   | Human exposure to radioactive agents?  Foetal tissue or abortus?  Investigational new device?  Specify: __________________  Existing data available from Co-investigator? | Human exposure to infectious agents?  Investigational new drug?  Existing data available via public archives/sources?  Pathological or diagnostic clinical specimen only?  Observation of public behaviour?  New treatment regime? | | --- | --- | | | | | | | | | | |

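### Two incompatible randomisation schemes are left open, and one prints its whole patterned A/B list in the protocol, so random, concealed allocation is not assured

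*Protocol*

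**What the plan says.** The Randomization section of the protocol first sets out a block plan: "We have a plan to make 17 blocks- 8 blocks of size 4, 4 blocks of size 6, 4 blocks of size 8, 1 block". That single last block has ten places. The section says of the content of the blocks: "Each “block” would have a specified number of randomly ordered treatment and placebo assignments". Figure 3 then prints that content by sex and by presenting criterion (low WLZ or MUAC, versus bilateral pedal oedema). The blocks of six read "AAABBB | BBBAAA | ABABAB | BABABA" and the blocks of eight "AAAABBBB | BBBBAAAA | ABABABAB | BABABABA"; in each, the first two are in the male column and the last two in the female column. The single block of ten is one alternating sequence spanning both columns.

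After the word *Or*, the next paragraph describes something else: a permuted-block sequence generated by computer, with concealment, prepared in advance by an independent researcher who has no part in the trial. It names no strata. On block size it says: "Reasonably large blocks with variable block sizes will be constructed to reduce the predictability".

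The meaning of the letters is given in two other places. Under Intervention: "L- carnitine oral solution (100mg/ml) for Group A", with placebo for Group B. In the sample-size table of the RRC application form: "Group A (Intervention arm)". The packaging text in the Intervention section mentions only a 100 ml bottle and gives no coding rule.

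**The concern.** A site cannot follow both schemes. They differ in stratification (sex and oedema against none named), in block size (eight of 17 blocks have size 4, against reasonably large ones) and in how the order within blocks arises (printed patterns against a computer-generated sequence). The printed scheme also contradicts its own promise of random order within blocks.

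The study physician enrols the child, and a study physician follows the child every day in the nutritional rehabilitation unit. If the coming assignment can be read from the protocol, enrolment can be steered and care can be influenced. The Data Analysis section compares the arms with simple two-group tests, and no analysis can repair selection at entry once children are enrolled.

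**Working it through.** **1. Is Figure 3 the whole list or a sample of it?** The block plan gives 8×4 + 4×6 + 4×8 + 1×10 = 32 + 24 + 32 + 10 = 98, in 8 + 4 + 4 + 1 = 17 blocks. Counting the sequences printed in Figure 3:

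- Low WLZ/MUAC, boys: 2×(4 + 6 + 8) = 36 places
- Low WLZ/MUAC, girls: 2×(4 + 6 + 8) = 36 places
- Block of ten, not tied to a sex: 10 places
- Oedema, boys: 2×4 = 8 places
- Oedema, girls: 2×4 = 8 places

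The total is 36 + 36 + 10 + 8 + 8 = 98. Every block is balanced, so this is 49 A and 49 B, which is the planned sample size. The table matches the plan block for block and reads as the complete list.

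**2. Is the order within blocks random?** The numbers of balanced orders for sizes 4, 6, 8 and 10 are C(4,2) = 6, C(6,3) = 20, C(8,4) = 70 and C(10,5) = 252. Figure 3 uses 4, 4, 4 and 1 of them. Every male sequence is a run (A's then B's, or the reverse). Every female sequence, and the block of ten, is strict alternation.

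**3. How predictable is the printed list?**

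- *Used in printed order:* 98 of 98 assignments are known in advance.
- *Blocks shuffled within each stratum* (assumption; the block of ten is treated as its own stratum). All orders were enumerated for an observer who knows the printed list and every earlier assignment in the stratum. Expected number certain: 26.17 + 27 + 10 + 7 + 7 = 77.17, and 77.17/98 = 79%. Expected number guessed correctly: 31.77 + 33.5 + 10 + 7.5 + 7.5 = 90.27, and 90.27/98 = 92%.
- *Random permuted blocks of sizes 4, 6 and 8* (assumed sizes), with an observer who always guesses the arm that is behind. Simulation gives about 67% correct with the same stratum sizes and 68% unstratified; pure chance is 50%.

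The last two results use different guessing rules. Under the simple guess-the-lagging-arm rule, the shuffled printed blocks give, stratum by stratum, (36×0.583 + 36×0.750 + 10×0.751 + 8×0.625 + 8×0.749)/98 ≈ 68%, the same as proper blocks. The excess predictability therefore comes from having the list, that is, from printing it.

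**4. Does the list fit the children who will come?** Oedema has 16 places, 8 per sex (16/98 = 16.3%). A ninth oedematous boy or a ninth oedematous girl has no place. With fewer than 16 oedematous children, the other 82 places cannot bring the total to 98. The Study Design section joins the criteria for severe acute malnutrition with *or*, and the Management section allows oedema together with low WLZ. A child with both fits two rows of Figure 3, and no rule decides between them.

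**The case against.** The strongest reply is that the paragraph after *Or* already describes a sound method: computer generation, concealment and an independent preparer. That stands. A reader might infer that allocation in this trial is neither random nor concealed. The documents do not support this, because it is true of the printed scheme only and nothing shows that the printed scheme will be the one used.

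Other parts of the reply also stand:

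- Saying which group receives active product is ordinary protocol content, and the key is in other sections, not beside the table. It harms blinding only if bottles or records carry A or B, and the protocol does not say that they do. The placebo is described as identical in appearance and taste.
- The order in which blocks are used is not stated, and an image at that point is not shown in the text at hand.
- Varying block size is not itself a contradiction, since the printed plan also varies size.

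Two further readings go too far. One is that a single unblinded child unblinds the list. If the printed order is known, nothing remains to be unblinded; if blocks are shuffled, one child reveals at most the rest of its own block. The other is that learning the size and first letter of each block gives away the remaining 98 − 17 = 81 assignments. The arithmetic is right, but it supposes that staff learn 17 assignments and block sizes despite masking, and the protocol gives no route for that.

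None of this removes the unresolved choice or the printed non-random sequences.

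**Conclusion.** The point holds in conditional form. The protocol permits two incompatible schemes and makes no choice, so random, concealed allocation is not assured. One permitted scheme prints a complete, patterned list that contradicts its own statement of random order.

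The size depends on use. It is 98 of 98 assignments known in advance if the printed order is followed. It is about 79% certain and 92% guessable if blocks are shuffled within strata and the observer knows the list and all earlier assignments; double blinding would limit that knowledge. Predictability creates an opportunity for selection bias. It does not show that the double-blind design or the between-group test has failed.

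This must be settled before enrolment, because it cannot be repaired afterwards.

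**What to change.** - Delete *Or*, the 17-block plan and the sequences in Figure 3.
- Keep only the scheme in the paragraph that follows: computer-generated random permuted blocks of varying size, with the list prepared and held by the independent researcher.
- Do not disclose block sizes in the protocol.
- Label bottles with participant-specific codes rather than A or B.
- Stratification is optional, since the retained scheme names no strata. If sex or oedema is wanted as a stratum, state it within that scheme, with one rule for children who meet both the oedema and the WLZ/MUAC criteria, and open-ended lists per stratum so that no child is left without a place.

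The cost is a change of wording, a new list and coded labels. The one downside is that the arms may end slightly unequal, for example 48:50 instead of 49:49.

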**Or,**

We will assign participants to the intervention or the control arm using permuted block randomization method with concealment to ensure that the allocation is not made before the participant has given their consent and joined the study. A random allocation sequence will be generated using a computerized random allocation system for permuted block randomization to ensure comparable allocation numbers at a certain equally spaced points in the sequence of patient assignment. A parallel type of randomization will be used. Reasonably large blocks with variable block sizes will be constructed to reduce the predictability. Random assignment will be prepared in advance by an independent researcher from icddr,b, who has no involvement with the trial.

**Anthropometric measurements**

All the measurements (length, weight, MUAC) will be taken at enrolment and on each day when the participants will receive intervention/placebo. If not possible, a one-day window period will be used. End-line anthropometry data will be collected on the 15th day of supplementation. In addition, we will measure anthropometry on the 180th day after the completion of supplementation to observe the long-term effect of the intervention on the rate of weight gain. Trained staff will take all the measurements as per the standard operating procedures (SOPs) and keep records in standard CRFs. Every measurement will be taken twice and the average will be documented. The Seca weighing scale will be used for weight measurement and Seca length board will be used for length measurement. To ensure the quality of anthropometric data, 5% of the participants will be measured second time within 24 hours of each data collection. Additionally, quality control assessment will be organized monthly and inter-rater reliability will be calculated to ensure the anthropometric data quality. Steps will be taken to minimize the discomfort and inconvenience of the participants during the anthropometric measurement.

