**Management**

Children will be given their first dose of supplementation when they would be considered improved, i.e. no diarrhea for last 24 hours, patient fulfill the criteria of NRU transfer (presence of oedema, or/and WLZ <-3SD, or/and WAZ <-4SD). At NRU after randomization trained research staff will observe each child for 60 minutes following ingestion of investigational product and record any adverse event- nausea, vomiting etc. Vomiting is defined as the forceful emptying of stomach contents and will be recorded if it happened within 60 minutes following the administration of investigational product. Children will get supplementation of investigational product in addition to standard of care at NRU for 15 days. Supplementation will be given at every 8 hours under supervision of a trained staff.

**Study Days**Patients will be followed up every day by a study physician at NRU for 15 days. Adverse events will be documented and drug accountability recorded. During this intervention period if study participants fulfill the discharge criteria of NRU (WLZ/WHZ ≥ -2SD, WAZ ≥ -3SD and oedema resolved), we will discharge the patient with remaining dose of the syrup and advise them to come for follow up into after completion of the remaining dose. This same method will be applicable for both the intervention arm and placebo arm.

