## Data Analysis

Data will be entered into the pre-tested case record forms(CRFs) using SPSS (20.0 version, Armonk, NY) and finally cleaned with a repeated check. Data will be presented using frequency with percentage for categorical variables. Mean with standard deviation will be used for symmetrical continuous variables. Median with interquartile range will be used for asymmetrical numeric variables. To know the outcome of the intervention in our study children bivariate, crude analyses of the association will be done that will involve Chi-square or Fisher’s exact test for comparing differences in proportion and t-tests for numeric variables between the groups. Nnonparametric continuous data will be analyzed by Mann-Whitney U-test. Results from all children will be included in the analysis of the study on an intention-to-treat basis. Data from children withdrawn because of failure to respond, or voluntary dropouts will be included in the analysis up to the time of withdrawal. A supplementary analysis excluding the children withdrawn may also be done. A probability of less than 0.05 will be considered statistically significant.

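### The end-line and 180-day weights are timed from taking and finishing the product, so a child who stops or leaves unrecovered has no clear day-15 weight and no day-180 date

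*Protocol*

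**What the plan says.** Under Anthropometric measurements, the routine schedule is: "All the measurements (length, weight, MUAC) will be taken at enrolment and on each day when the participants will receive intervention/placebo", with a one-day window. The primary time point is "End-line anthropometry data will be collected on the 15th day of supplementation". For the long term, "we will measure anthropometry on the 180th day after the completion of supplementation". Drug accountability repeats both anchors: "They will be evaluated by measuring the rate of weight gain at 15 days of supplementation and 180 days of completion of supplementation".

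The Study Days paragraph under Management covers leaving before day 15 in one situation only: "During this intervention period if study participants fulfill the discharge criteria of NRU", meaning recovery of weight-for-length and weight-for-age z-scores and resolved oedema. These children take the remaining doses home, and staff "advise them to come for follow up into after completion of the remaining dose". The ERC Abstract Summary and the reply to the Research Review Committee say the same. The Study Days paragraph also has a physician see patients daily in the unit for 15 days, but names no weight.

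Data Analysis states: "Results from all children will be included in the analysis of the study on an intention-to-treat basis". It then says that children withdrawn for failure to respond, and voluntary dropouts, contribute data only until they withdraw. Failure to respond is not defined. The Safety Plan records the reasons for and timing of dropouts.

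**The concern.** An intention-to-treat comparison needs the outcome to be sought in every randomised child at times that do not depend on what happened after randomisation. Here the times are defined by exposure. A child who takes no product after day 5 has no later product day, does not literally reach a 15th supplementation day, and has no completion date.

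The one provision for leaving early is triggered largely by weight recovery, which is closely bound to the primary outcome, the rate of weight gain. One withdrawal reason, failure to respond, is close to that outcome as well. Whether a child has a later weight can therefore depend on how well the child gained or tolerated the syrup, and either may differ by arm. The visible text never separates stopping the product from leaving the study. An analysis plan can choose a method for missing values, but it cannot supply weights that the protocol never asked staff to take.

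**Working it through.** **1. What the schedule gives each kind of child**

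| Child | Daily weights | Day-15 weight | Day-180 weight |
|---|---|---|---|
| Completes 15 days in the unit | all 15 days | scheduled | dated from completion |
| Discharged early on meeting criteria | up to discharge | advised to return after the last dose | dated from completion |
| Stops product, stays in the unit | up to the last product day | seen daily by a physician, no weight named | no completion date |
| Leaves before meeting criteria | up to departure | no return visit | no completion date |
| Withdrawn for failure to respond | up to withdrawal | none scheduled | no completion date |

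The last three rows are the gap.

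**2. The plan's sample size**

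Inputs are from the Sample Size section: δ = 2.4, δ₀ = 0.1, S = 4.3, z-values 1.645 and 0.845, attrition 10%. The fraction in the formula is a figure not shown, so the denominator δ − δ₀ is inferred.

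n = 2 × (2.49 / 2.3)² × 4.3² = 43.34, rounded up to 44. Then 44 / 0.9 = 48.9, rounded up to 49.

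The stated 49 per arm reproduces. With 10% lost, 49 × 0.9 = 44.1 per arm remain, so the planned attrition covers precision. It does nothing about which children are lost.

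**3. Effect of selective loss on the difference**

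Assume that gain Y is normal with SD 4.3, mean 0 on placebo and 2.4 on active. A child is lost when a score ρY/4.3 + √(1 − ρ²)e falls below a cut-off c, where e is standard normal and c is set so that 10% are lost overall. ρ is the assumed within-arm correlation of the score with gain. With a = c − ρμ/4.3, where μ is the arm's mean gain:

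loss = Φ(a); mean of measured children = μ + 4.3ρ φ(a) / (1 − Φ(a)).

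| ρ (assumed) | a placebo / active | Loss placebo / active | Mean placebo / active | Difference |
|---|---|---|---|---|
| 0 | −1.28 / −1.28 | 10% / 10% | 0 / 2.40 | 2.40 |
| 0.3 | −1.202 / −1.370 | 11.5% / 8.5% | 0.28 / 2.62 | 2.34 |
| 0.5 | −1.154 / −1.434 | 12.4% / 7.6% | 0.50 / 2.73 | 2.23 |
| 1 (all losses the poorest gainers) | −1.052 / −1.610 | 14.6% / 5.4% | 1.16 / 2.90 | 1.74 |

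The attenuations are 0%, 3%, 7% and 27%. At ρ = 1 with 5% or 15% lost overall, the difference is 1.97 or 1.57.

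**4. Direction**

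If lost children would have gained g less than measured children in the same arm, the comparison of measured children shifts by (p_active − p_placebo) × g, where p is the share lost.

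- Assumed loss 5% active, 15% placebo, g = 4.3: −0.10 × 4.3 = −0.43, so 2.4 becomes 1.97.
- Loss reversed (15% active, 5% placebo, for example through vomiting): +0.43, so 2.4 becomes 2.83.
- For g from 2.4 to 8.6, the shift is 0.24 to 0.86 either way, or 10% to 36% of 2.4.
- Equal loss and equal g in both arms: no shift.

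If the children lost are instead good gainers who went home and did not return, g is negative and the signs flip.

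**The case against.** Four points weigh on the other side.

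- **Data exist.** A reader might infer that these children have no outcome at all. They do not lack one entirely: enrolment and daily weights up to stopping are taken and kept, and the primary outcome is a rate, so a shorter, child-specific rate can be computed. This stands. That rate covers a different period from the day-15 outcome, however, and offers nothing at day 180.
- **The day-15 anchor can be read loosely.** In a fixed 15-day course, the 15th day of supplementation may simply mean study day 15, and a child who stays in the unit is seen daily. This is fair, and is why the day-15 weight is called not clearly scheduled rather than absent. No such reading rescues the day-180 date for a child who never completes.
- **Direction and size.** A reader might infer that the schedule shrinks the effect by 27%. The documents do not support that. A slow gainer who stays is weighed on site, while the good responder sent home is only advised to return. Vomiting is an expected adverse event and could raise loss on active. The 27% needs every lost child to fall below one common gain cut-off and to contribute nothing.
- **Visibility.** The workflow figure and some pages are not shown, so the absence of a rule is established only for the visible text. How missing values are analysed may also sit in an unseen analysis plan. Who is weighed and when is a protocol matter.

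**Conclusion.** The point holds as a gap in data collection, not as a demonstrated bias. As written, a child who stops the product, is withdrawn for failure to respond, or leaves before meeting discharge criteria has weights only to that point, no clearly scheduled day-15 weight and no defined day-180 date. The intention-to-treat promise is weakened accordingly.

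The consequence has no fixed direction or size. On the plan's own 2.4, 4.3 and 10%, the difference among measured children runs from 2.4, through about 2.2 to 2.3, down to 1.74 in the worst case for loss of poor gainers. Loss that is heavier on active, or loss of good gainers, could push it above 2.4. The correlations, the split of loss between arms and the gain deficit g are assumptions; the protocol gives only the overall attrition. The sample size is unaffected. The change is worth making because it is cheap beforehand and the weights cannot be recovered afterwards.

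**What to change.** **Drug accountability and Anthropometric measurements.** Count the weights from randomisation or first dose: daily while in the unit, day 15 with the existing one-day window, and the long-term visit at day 195 (15 + 180). State that they apply to every randomised child, whatever the product use and however the child left, unless consent to follow-up is withdrawn.

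**Management and Data Analysis.** Record stopping the product separately from withdrawal from follow-up. Treat failure to respond, intolerance and early departure as reasons to document, not as reasons to end measurement. Invite children who leave without meeting the discharge criteria to the same day-15 and long-term visits as those who met them.

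**Cost.** This is a wording amendment to four sections, plus some extra return visits, calls and travel allowances for at most about 10 of 98 children at the planned attrition (0.10 × 98 = 9.8). The ERC Abstract Summary promises travel allowances for follow-up, but the budget shows no separate line for them, so that needs checking. Some of these visits will not be achieved. No dosing, discharge or stopping rule is changed.
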